#### Interventions

##### Active Intervention (Climate Schools Plus Group)

###### Climate Schools Plus: Student Component

The student component of the intervention consists of the effective and validated *Climate Schools: Alcohol* and modules [18-21,23,24,37], which involve 12, 40-minute lessons aimed at reducing alcohol and cannabis use and related harms. The first 6 lessons focus specifically on alcohol and are delivered in year 8, the remaining 6 lessons focus on alcohol and cannabis and are delivered 12 months later when the students are in year 9, prior to the development of harmful patterns of alcohol and cannabis use [38]. Therefore, the *Climate Schools* lessons are designed to avoid the development of harmful use by intervening when students are aged 12-14 years. The program will be completed at school, during regularly scheduled PDHPE classes, and to access the material, teachers, parents, and students are asked to create unique confidential log-in details on the CSP study website. The first part of each *Climate Schools* lesson is in the form of an internet-based cartoon storyline completed individually by students, which imparts information about alcohol (in years 8 and 9) and cannabis (in year 9; see Figure 2 for an example of the cartoon content). The second part of each lesson consists of optional class activities delivered by the teacher, such as role-plays and group discussions, which reinforce the information in the cartoons and allow communication among students. Teachers are provided access to an internet-based teacher’s manual, which contains lesson activities, implementation guidelines, links to the syllabus, and teacher summaries for each lesson.

**Figure 2 figure2:**
[figure not shown]
Screenshot of example student cartoon. Source: Netfront Pty Ltd.

###### Climate Schools Plus: Parent Component

The parent component was developed in consultation with parents of Australian secondary school students and relevant experts through a large scoping survey, beta-testing, and pilot-testing of the developed program [16]. At the beginning of the study, parents will be sent an email from their school with information about the CSP program and instructions on how to register. Once parents have registered with their username, password, and unique school code, they will have access to 2 webinars (approximately 5 minutes each, at the beginning of years 8 and 9). These webinars are hosted by CC, who is a senior research fellow at the National Health and Medical Research Council (NHMRC) Centre of Research Excellence in Mental Health and Substance Use and also a member of the research team. The webinars provide overviews of alcohol and cannabis use in adolescents and related harms and highlight the role parents can play in preventing substance use in their child. During the webinar, parents will also be encouraged to engage in the “rule-ranking” component of the program, which allows parents from the same school to rank a series of rules related to alcohol use (eg, “Any alcohol in the family home is strictly off-limits to adolescents and their friends”); this component aims to facilitate a collective understanding of alcohol prevention and the role parental rule-setting plays in prevention by facilitating agreement among parents on a shared set of rules, which they can implement on their adolescents as a group. The top 3 rules will be published after 6 weeks, and parents will be encouraged to view and implement these rules with their adolescents over the school year (see Figures 3 and 4 for example screenshots of these components).

**Figure 3 figure3:**
[figure not shown]
Screenshot of the year 8 webinar. Source: Netfront Pty Ltd.

**Figure 4 figure4:**
[figure not shown]
Screenshot of the rule-ranking component (when top 3 rules have been finalized). Source: Netfront Pty Ltd.

Parents will also have access to 6 brief internet-based modules (under 10 minutes each, 4 in year 8 and 2 in year 9) covering a range of topics about alcohol and cannabis use, as well as parenting strategies and communication tips (Textbox 1; Figure 5). Parents can access the year 8 content anytime over the course of the study, whereas the year 9 content will be locked until the beginning of 2019. Parents will be sent occasional reminders through their school and the CSP website informing them when new content is available. Parents will also be emailed weekly summaries of the content covered in each of the *Climate Schools* student lessons. Figure 6 provides further information regarding the parent intervention and how it relates to the outcomes of the study.

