The parent component for the CSP program is based on the successful Dutch Prevention of Alcohol Use in Students (PAS) program [31-33] and was adapted for Australia in consultation with Australian parents and education and health experts [16]. The parent component of the CSP program is designed to be delivered entirely online, across the same school terms as the student *Climate Schools* program. The parent component targets modifiable parenting factors associated with adolescents’ alcohol and cannabis initiation and misuse [10,34], including rule-setting, parental supply, modeling, and monitoring. The parent component comprises introductory webinars, a rule-ranking component, internet-based modules, and internet-based parent summaries of the material covered in the student program. A complete description of the parent component can be found in a development paper published by the members of the research team [16].

Currently, we are seeking to evaluate the effectiveness of the CSP program in preventing alcohol and cannabis use and increasing parents’ self-efficacy to prevent their child from using these substances. Incorporating an internet-based parent component into an effective school-based student program has the potential to remarkably enhance prevention outcomes and reduce alcohol- and cannabis-related harms among adolescents.

We will determine the effectiveness of the CSP intervention by running a cluster RCT in Australian Independent and Catholic secondary schools (ACTRN12618000153213). Cluster randomization will be used to avoid contamination of the control group with the intervention groups through student and staff communication. Schools will be randomly allocated to the CSP condition or the “control” condition. Students and parents in the CSP condition will be provided access to the *Climate Schools*: *Student* component and the *Climate Schools Parenting Program*, respectively, whereas students in the control condition will receive their health education classes as usual, which covers alcohol and other drug education topics. Students and parents in both groups will complete self-report surveys at baseline and 12 and 24 months postbaseline. Figure 1 depicts the study design.

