#### Participant Timeline

Students and parents in the CSP group will be invited to register for the CSP program online during the first year of the study (for the majority of schools, this will be during term 1 of 2018; however, for some, it will be term 2 or 3 of 2018). Students will complete their registration and baseline survey during their regularly scheduled PDHPE classes, and their teachers will facilitate their progression through the *Climate Schools: Alcohol* lessons. During the first week of the intervention, parents register for the program and are invited to view the webinar, participate in the interactive rule-ranking component, and explore the available modules. Approximately 8 weeks after registering for the program, parents and students will be prompted to complete an evaluation of the program content online, through the CSP website. Similarly, in 2019, students will complete the 12-month follow-up questionnaire, and their teacher will facilitate their progression through the lessons. Simultaneously, parents of these students will be invited to view the second webinar, the second round of rule-ranking, and invited to explore year 9 parent modules. Students and parents will also be asked to complete an evaluation of the year 9 program through the CSP website, as they did in the previous year. Finally, in 2020, parents and students will be asked to complete the 24-month follow-up questionnaire; a reminder email will be sent to nonresponding parents and students 1 week after they are invited to complete it and another reminder 1 week later. Table 1 summarizes the student and parent involvement in the study.

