##### Secondary Outcomes

All secondary outcomes will be assessed at baseline and 12- (prior to the delivery of the year 9 intervention) and 24-month follow-up, except for cannabis-related knowledge and patterns of cannabis use, which will only be measured at 12- and 24-month follow-up.

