## Results

This study is funded by the Australian Government Department of Health from 2016 to 2020 and by Society for Mental Health Research Early Career Research from 2015 to 2017. Enrollment of schools began in January 2018, with 8 out of 12 schools enrolled at the time of submission (enrollment is expected to be complete by October 2018). Baseline assessments are currently underway, and the first results are expected to be submitted for publication in 2019.

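### Year 9 parent content unlocks on one calendar date, which does not secure the stated pre-year-9 timing of the 12-month parent survey in schools that start in term 2 or 3 of 2018

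*Protocol article*

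**What the plan says.** Four statements in the protocol article fix the timing.

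- **Release of content** (Methods, Climate Schools Plus: Parent Component): "the year 9 content will be locked until the beginning of 2019". The same paragraph says that parents are reminded when new content becomes available.
- **Order of measurement** (Secondary Outcomes): "All secondary outcomes will be assessed at baseline and 12- (prior to the delivery of the year 9 intervention) and 24-month follow-up". The exceptions are cannabis knowledge and cannabis use, which are measured only at 12 and 24 months. Parent self-efficacy, supply, communication and knowledge are among the secondary outcomes.
- **Follow-up clock** (Introduction, repeated under Data Collection): "Students and parents in both groups will complete self-report surveys at baseline and 12 and 24 months postbaseline".
- **Staggered start** (Participant Timeline), on registration in CSP schools: "for the majority of schools, this will be during term 1 of 2018; however, for some, it will be term 2 or 3 of 2018".

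Two further places bear on the sequence. For 2019, Participant Timeline names the students' 12-month questionnaire and lessons and continues: "Simultaneously, parents of these students will be invited to view the second webinar, the second round of rule-ranking, and invited to explore year 9 parent" content. It does not mention the 12-month parent survey at that point. Table 1 gives one schedule for all schools. It places parent survey 2 in Term 1, 2019, in the row above the year 9 parent modules.

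**The concern.** The release rule runs on the calendar and the survey rule runs on each school's baseline. For a school that starts late in 2018 the two drift apart. The content is then open well before the survey that is meant to come first. Control parents have no access to this content during the trial, so any early exposure is confined to the CSP arm.

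The outcome most at risk is parents' cannabis knowledge. Parent modules 5 and 6 cover cannabis, and the 12-month wave is the first time this knowledge is measured. Statistical Analysis names the intervention-by-time interaction as the effect of highest interest. With only two waves, that interaction takes the 12-month value as its starting point. For parental self-efficacy, supply and communication, the 12-month contrast would no longer be the effect of the year 8 programme alone. It would mix parents with and without year 9 exposure.

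**Working it through.** No sample size or power figure in the protocol bears on this point, so there is none to reproduce. The check is calendar arithmetic.

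**Inputs from the protocol:** unlock at the beginning of 2019; starts in term 1, 2 or 3 of 2018; survey 12 months after baseline; Table 1 slot in Term 1, 2019.

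**Assumptions, not in the protocol:** unlock between 1 January and 1 February 2019; in 2018, term 1 runs 1 February to 13 April, term 2 runs 1 May to 6 July and term 3 runs 24 July to 28 September; term 1 of 2019 runs 1 February to 12 April; one month is 30.44 days.

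**Step 1. Survey held at a true 12 months.** Time open before the survey = (baseline + 12 months) − unlock date. The shortest case pairs the first day of term with a 1 February unlock. The longest pairs the last day of term with a 1 January unlock.

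| Start in 2018 | Shortest | Longest |
|---|---|---|
| Term 1 | 0 days = 0 months | 102/30.44 = 3.4 months |
| Term 2 | 89/30.44 = 2.9 months | 186/30.44 = 6.1 months |
| Term 3 | 173/30.44 = 5.7 months | 270/30.44 = 8.9 months |

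**Step 2. All parents surveyed in Term 1, 2019, as in Table 1.** Interval from baseline = survey date − baseline date. The shortest case is 1 February 2019 minus the last day of the start term. The longest is 12 April 2019 minus the first day.

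| Start in 2018 | Shortest | Longest |
|---|---|---|
| Term 1 | 294/30.44 = 9.7 months | 435/30.44 = 14.3 months |
| Term 2 | 210/30.44 = 6.9 months | 346/30.44 = 11.4 months |
| Term 3 | 126/30.44 = 4.1 months | 262/30.44 = 8.6 months |

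Under this reading the content is open before the survey for at most 101/30.44 = 3.3 months (1 January to 12 April 2019). For term 2 and 3 starters, however, the whole range lies below 12 months.

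**Step 3. Direction of bias for parent cannabis knowledge.** Let p be the share of CSP parents who used modules 5 and 6 before survey 2, and g their average knowledge gain. The two-wave effect is D = (CSP at 24 − CSP at 12) − (control at 24 − control at 12). Early use raises only the CSP 12-month mean, by p × g, so the estimate becomes D − p × g. If g is positive, this is a shift toward no effect. If p is zero, there is no bias. The protocol gives neither p nor g, so no size is put on the shift. The plain between-group difference at 24 months does not contain the 12-month value and is not shifted.

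**Step 4. After the change proposed below.** If a school's unlock follows its own survey window, the time open before the survey is 0 months for every survey returned within the window, whatever the start term.

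**The case against.** The strongest reply is that access is not use. The calendar rule gives only the earliest opening date, and nothing in the protocol says that parents look at year 9 material before survey 2. Secondary Outcomes states the intended order, and Table 1 lists the survey above the modules. Participant Timeline ties the year 9 invitation to the students' follow-up wave, not to 1 January. The website may also prompt the survey at login, a detail that an article can leave out. For term 1 starters, the majority, unlock and survey can nearly coincide. All of this stands, and it limits the point to what can happen. It does not remove it: for late starters, no stated mechanism makes the calendar unlock, the 12-month clock and the survey-first order hold together.

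Several stronger readings are tempting, and the protocol does not support them.

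- A reader might infer that 12-month parent measures in CSP schools are in general taken after exposure. The text shows only that they can be.
- A reader might take "enrollment is expected to be complete by October 2018" as a baseline date and stretch the gap further. It refers to enrolment of schools. The latest start that Participant Timeline gives is term 3.
- A reader might see the same fault at baseline, because "Once parents have registered with their username, password, and unique school code, they will have access to 2 webinars". That makes registration a condition of access. It does not place content before survey 1, which Table 1 lists first.
- A reader might express the bias as a fraction of the 0.2 standardized difference under Sample Size. That target belongs to the primary outcomes in students. Uptake, module effect and the share of late CSP schools are not given.

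**Conclusion.** The point holds as a conflict between stated rules that needs to be reconciled. For CSP schools starting in term 2 or 3 of 2018, year 9 parent content can be open about 3 to 6 or 6 to 9 months before a true 12-month parent survey. Keeping to Term 1, 2019 instead puts that survey at about 7 to 11 or 4 to 9 months after baseline. These ranges rest on the assumed term dates and unlock date. The conflict itself needs only that some CSP schools start well after term 1.

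What is at stake is limited to 12-month parent secondary outcomes and the models that use them, parent cannabis knowledge above all. Any bias arises in one arm and, for that outcome, pulls the 12-to-24-month contrast toward no effect by an amount that the protocol does not allow one to estimate. The student primary outcomes at 24 months are not directly affected. The change is worth making because it is cheap. The trial's main conclusion does not depend on it.

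**What to change.** 1. Replace the calendar unlock with a per-school unlock, set after that school's 12-month parent survey window closes. Use the same window length in both arms.
2. Send the year 9 parent invitations and reminders only after that unlock.
3. Reconcile Parent Component, Participant Timeline, Secondary Outcomes and Table 1 for late-starting schools. State whether their survey 2 follows the 12-month clock or the Term 1, 2019 slot.
4. Extend the tracking described under Intervention Fidelity to record dates of access, and report how many CSP parents opened year 9 content before completing survey 2. Keep those parents in the intention-to-treat analysis. Removing them would drop the more engaged parents from one arm only.

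An individual lock that opens on submission of the survey is not advised. It would give CSP parents a reason to respond that control parents lack. A window set by school avoids this. Surveys returned after the window can still follow exposure, and the count in item 4 would show how many.

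The cost is a change of setting in an existing website lock and a few sentences of protocol text. The downside is that parents in some schools see year 9 content somewhat later. In return, release would follow each school's own timetable, in keeping with the Introduction, which has the parent component run across the same terms as the student programme.

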##### Control Group

Students and their parents will follow the same registration and consent process in both the control group and the CSP group and will be asked to complete the baseline questionnaire. Then, students will receive their regular drug and alcohol education during their PDHPE classes (ie, they will cover topics such as drug use, health and well-being, sources of support, personal safety, exploring risk, etc, in accordance with the student outcomes defined by the Australian National Health and Physical Education syllabus) during the study. These students will be asked to complete the 12-month follow-up questionnaire in 2019 and the final follow-up questionnaire in 2020. Similarly, parents in the control group will be asked to complete the baseline questionnaire and 12- and 24-month follow-up questionnaires over the same period.

#### Participant Timeline

Students and parents in the CSP group will be invited to register for the CSP program online during the first year of the study (for the majority of schools, this will be during term 1 of 2018; however, for some, it will be term 2 or 3 of 2018). Students will complete their registration and baseline survey during their regularly scheduled PDHPE classes, and their teachers will facilitate their progression through the *Climate Schools: Alcohol* lessons. During the first week of the intervention, parents register for the program and are invited to view the webinar, participate in the interactive rule-ranking component, and explore the available modules. Approximately 8 weeks after registering for the program, parents and students will be prompted to complete an evaluation of the program content online, through the CSP website. Similarly, in 2019, students will complete the 12-month follow-up questionnaire, and their teacher will facilitate their progression through the lessons. Simultaneously, parents of these students will be invited to view the second webinar, the second round of rule-ranking, and invited to explore year 9 parent modules. Students and parents will also be asked to complete an evaluation of the year 9 program through the CSP website, as they did in the previous year. Finally, in 2020, parents and students will be asked to complete the 24-month follow-up questionnaire; a reminder email will be sent to nonresponding parents and students 1 week after they are invited to complete it and another reminder 1 week later. Table 1 summarizes the student and parent involvement in the study.

#### Ancillary or Posttrial Care

Upon conclusion of the trial, all schools in the control group will receive access to the same materials offered to the CSP group, free of charge.

Overview of content in *Climate Schools Plus* parent modules.Module 1: Prevalence, patterns, and harms of adolescent alcohol useModule 2: Parental attitudes and rule-settingModule 3: Parental supply and useModule 4: Communication and involvementModule 5: Prevalence, patterns, and harms of adolescent cannabis useModule 6: What parents can do to prevent adolescent cannabis use

**Figure 5 figure5:**
[figure not shown]
Screenshot of one of the parent modules (Parent Module 4, in the year 8 program). Source: Netfront Pty Ltd.

#### Outcomes

We selected the following primary outcomes to reflect the overall target of the intervention (ie, to prevent alcohol use and related harms in adolescents). All primary outcomes will be measured at baseline and 12- (prior to the delivery of the year 9 intervention) and 24-month follow-up, with the primary endpoint being 24 months.

##### Primary Outcomes

###### Any Alcohol Use

Any alcohol use is defined as the consumption of at least 1 full serve or standard drink of alcohol (ie, any drink containing 10 grams of alcohol). To measure this outcome, students would be provided with a chart used to illustrate a standard drink (as used in the NHMRC Australian Guidelines [39]) and asked *“Have you ever had at least one standard alcoholic drink?”* and *“Have you had at least one standard alcoholic drink in the past 12 months?”* Responses to both questions are in the form of “Yes” versus “No.”

###### Any Drinking to Excess

Any drinking to excess is defined as the consumption of ≥5 standard drinks on a single occasion, in line with the NHMRC Australian Guidelines for risky drinking on a single occasion [39]. These alcohol use measures were used in the National Drug Strategy Household Survey [4], the Australian Secondary Students Alcohol and Drug Survey [38], and previous *Climate Schools* trials [18-21,23,24,37] and allows for comparisons between this sample and a large-scale representative group of Australians. Specifically, students would be asked *“Have you ever had 5 or more standard alcoholic drinks on one occasion?”* and *“Have you had 5 or more standard alcoholic drinks on one occasion in the past 12 months?”* Responses to both questions are in the form of “Yes” versus “No.”

##### Secondary Outcomes

All secondary outcomes will be assessed at baseline and 12- (prior to the delivery of the year 9 intervention) and 24-month follow-up, except for cannabis-related knowledge and patterns of cannabis use, which will only be measured at 12- and 24-month follow-up.

